**CUTANEOUS VACCINE REACTIONS**

| Reaction                                                                                                 | Mild                                                                                                                                                                                                        | Moderate                                                                                                                                                                                                                                                                                   | Severe                                                                                                                                                                                                      | Extreme                                    |
|-----------------------------------------------------------------------------------------------------------------|--------------------------------------------------------------------------------------------------------------------------------------------------------------------------------------------------------------------|---------------------------------------------------------------------------------------------------------------------------------------------------------------------------------------------------------------------------------------------------------------------------------------------------|--------------------------------------------------------------------------------------------------------------------------------------------------------------------------------------------------------------------|---------------------------------------------------|
| Immediate reactions (within 6 hours of injection)                                                               | Symptoms of irritation locally (usually itching at the injection site)
OR
Erythema +/- swelling at the injection site                                                                                        |                                                                                                                                                                                                                                                                                                   | Laryngeal oedema insufficient to require intubation; diarrhoea insufficient to require IV fluids, or asthma insufficient to require hospitalisation
OR
Urticaria, angio-oedema
OR
Generalised pruritus | Anaphylactic shock                                |
| Delayed reactions                                                                                               | Erythema at injection site
Erythema up to and including 50% of baseline arm circumference
OR
Symptoms of irritation that are easily tolerated and do not require repeated medication
OR
Both | Erythema at injection site
Erythema greater than 50% of the arm circumference at baseline
With or without
Symptoms of irritation that do not require repeated medication
OR
Symptoms of irritation that require repeated medication
AND erythema up to and including 50% | Erythema at injection site
Erythema greater than 50% of the arm circumference at baseline AND symptoms of irritation requiring repeated medication                                                       | Hospitalisation                                   |
|                                                                                                                 | Blistering or ulceration at injection site
Fluid filled vesicles or superficial disruption of epithelium covering an area < 1cm                                                                          | Blistering or ulceration at injection site
Fluid filled vesicles or superficial disruption of epithelium, area 1 - 2cm
OR
Blood filled vesicles
OR
Full thickness disruption of epithelium healed within 2 weeks                                                            | Blistering or ulceration at injection site
Full thickness disruption of epithelium not healed within 2 weeks                                                                                             | Necrosis                                          |
| Intramuscular vaccination                                                                                       | Soft swelling – local
Swelling <25% of arm or leg                                                                                                                                                        | Soft swelling – local
Swelling 25-50% of arm or leg                                                                                                                                                                                                                                     | Soft swelling – local
Swelling >50% of arm or leg
Or
Induration/hardened swelling
(when considered by the clinician to be associated with a process arising in the muscle)        |                                                   |
| Intradermal vaccination, or attributable to leakage of material into the dermis after intramuscular vaccination | Induration/hardened swelling
Induration
Diameter < 1.5cm                                                                                                                                              | Induration/hardened swelling
Induration
Diameter 1.5 – 3cm
And
Lasting for > 6 days                                                                                                                                                                                            | Induration/hardened swelling
Induration
Diameter > 3cm
And
Lasting for > 6 days                                                                                                                 | Necrosis                                          |
|                                                                                                                 | Generalised rash
Scattered (< 5 sites) maculo-papular rash AND no symptoms                                                                                                                     | Generalised rash
Scattered macular or papular rash AND symptoms
OR
Widespread rash AND not requiring repeated medication for symptoms                                                                                                                                      | Generalised rash
Widespread rash AND symptoms requiring repeated medication
OR
Involving mucous membranes (Stevens-Johnson reaction)                                                        | Generalised rash
Exfoliative dermatitis |

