## 1.5 End-points

### 1.5.1 Primary

The primary endpoints are immunogenicity and safety as defined below.

The primary immunogenicity parameter will be the presence of CD8/CD4+ T cell responses defined according to internationally agreed criteria for evaluation of IFN $\gamma$  ELISPOT assays (see section 8),

- in response to *env plus* at least one of the *gag, pol, nef* peptide pools
- at weeks 26 or 28

The primary safety parameters will be graded according to appendix 4, and are:

- Grade 3 or above local adverse event (pain, cutaneous reactions including induration)
- Grade 3 or above systemic adverse event (temperature, chills, headache, nausea, vomiting, malaise, and myalgia)
- Grade 3 or above other clinical or laboratory adverse event confirmed at examination or on repeat testing respectively.
- Any event attributable to vaccine leading to discontinuation of the immunisation regimen.

Note of clarification 8th Nov 2006: This will capture all Serious Adverse Events (SAE) as defined by ICH GCP as well as other grade 3 and 4 events that do not meet the criteria of an ICH GCP SAE.

Data on local and systemic events listed above will be solicited with specific questions or using a diary card for a minimum of 7 days following each immunisation. Data on other clinical events and laboratory events will be collected with an open question at each visit and through routine scheduled investigations respectively.

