## **4 Assessments**

### **4.1 Safety assessments**

#### **4.1.1 Local adverse events**

Pain in the muscle injected will be graded by the participant according to the criteria in appendix 4 as mild (1) moderate (2), severe (3) or extreme (4) and recorded in the appropriate case record form or once the participant has left clinic, in the diary card.

Redness will be recorded as the maximum diameter and expressed as a proportion of the arm or thigh circumference and graded on this criteria and the presence of symptoms according to appendix 4. Arm circumference will be measured at screening at the point one third of the way down from the acromio-clavicular joint towards the elbow joint of the non-dominant arm, and thigh circumference half way between the iliac promontory and the patella. Participants will be asked to record the maximum diameter in the diary card, as well as the presence of any itching or other discomfort and any medication taken for relief of symptoms.

Blistering (vesiculation) or ulceration will be graded according to size, depth, time to healing and character of blisters (blood-filled).

The presence of induration (hardened swelling) following intramuscular injection will be considered grade 3 if considered by the clinician to have arisen from a pathological process within the muscle. Induration considered in the judgement of the clinician to result from product leaking into the intradermal or subcutaneous layers will be graded according to the intradermal parameters in the toxicity table (Appendix 4). Soft swelling local to the injection site is not considered induration and should be graded according to the soft swelling parameters in the toxicity table (Appendix 4).

Clinical staff will complete the case record form following each immunisation. Completed case record forms and the diary cards will be sent to the data coordination centres to be recorded on the database. In the event that there are two observations on the same day, those confirmed at a visit will take precedence over diary card observations in the analysis.

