### 8.2 Primary analysis

The immunological end-points will be considered present or absent according to standardised operating procedures which take the background activity into account ( $> 4$ -fold the negative control and  $> 55$  Spot forming units/ $10^6$  cells). In both EV01 and EV02, a small proportion ( $<5\%$ ) of subjects showed persistent IFN $\gamma$  ELISpot reactivity to peptide pools prior to vaccination and subsequently across several timepoints. Subjects with IFN $\gamma$  ELISpot reactivity to peptide pools prior to vaccination will be considered to have non-specific cross-reactive responses to the peptide pools, and will be excluded from the immunogenicity analysis. The two groups DNAX2 and DNAX3 will be compared in terms of the proportion responding to *env* plus *gag/pol/nef* using a Chi-square test.

All safety end-points will be graded by the Clinical Investigators and reviewed by the Operational Sub-Group. Any queries about grade and relationship to study product that cannot be resolved will be referred to the Trial Coordinating Committee for a final decision. For the primary analysis of safety endpoints (as defined in section 1.5.1), results will be expressed as a proportion and the two groups compared using Fisher's exact test.

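### Appendix 4 grades thigh redness on arm circumference, against section 4.1.1, and its induration and blister rows leave some larger lesions without a grade

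*Protocol*

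**What the plan says.** Section 1.5.1 states that "The primary safety parameters will be graded according to appendix 4". Its first component is "Grade 3 or above local adverse event (pain, cutaneous reactions including induration". Section 8.2 adds that "results will be expressed as a proportion and the two groups compared using Fisher's exact test". Appendix 4 is therefore part of the definition of a primary endpoint.

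**Redness.** Section 4.1.1 says redness is recorded as a maximum diameter, "expressed as a proportion of the arm or thigh circumference and graded on this criteria" together with symptoms, and it has thigh circumference measured as well as arm circumference. The erythema cells of Appendix 4 (Cutaneous vaccine reactions) name only the arm. The severe cell reads "Erythema greater than 50% of the arm circumference at baseline AND symptoms of irritation requiring repeated medication". Section 2.3.1 puts every DNA-C dose into the two thighs.

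**Induration.** Section 4.1.1 and Appendix 4 make induration judged to arise in the muscle grade 3, whatever its size or duration. Section 4.1.1 sends induration attributed to product leakage to the intradermal row. There, grade 1 is a diameter under 1.5 cm with no duration condition, grade 2 is "Induration Diameter 1.5 – 3cm And Lasting for > 6 days" and grade 3 is "Induration Diameter > 3cm And Lasting for > 6 days".

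**Blistering.** Superficial or fluid-filled lesions under 1 cm are grade 1. The moderate cell covers "Fluid filled vesicles or superficial disruption of epithelium, area 1 - 2cm", blood-filled vesicles of any size, and full-thickness loss that heals within two weeks. Grade 3 is full-thickness loss still open after two weeks.

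**The concern.** A grading table used for an endpoint should give each reaction exactly one grade, and a larger lesion should not drop out while a smaller one is counted. The cutaneous table fails on both counts.

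The redness conflict gives the same reaction two grades, and one of the two disagreements falls at the grade 3 cut-off of the primary safety endpoint. The affected site is injected more often in DNAx3 than in DNAx2. Section 1.2.1 makes the trial open to investigators, and section 8.2 has them assign the grades, so the choice between the two readings is made by someone who knows the allocation.

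The induration and blister gaps leave some lesions with no grade at all. That affects the secondary endpoint of all grade 1 and 2 events (section 1.5.2) and the tables by maximum grade (section 8.3.2).

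**Working it through.** The plan gives no figure on this point to reproduce. The check treats each row as a rule and asks how many grades a given lesion receives.

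**1. Thigh redness under the two references.** By the Appendix 4 structure, with diameter *d* and reference circumference *C*:
- *d* above 0.5 × *C* with symptoms needing repeated medication: grade 3
- only one of those two conditions met: grade 2
- neither met: grade 1

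Appendix 4 sets *C* to the arm. Section 4.1.1, read as the injected limb, sets *C* to the thigh. The two disagree when 0.5 × arm < *d* ≤ 0.5 × thigh. The protocol gives no circumferences, so these are assumed:

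| Arm / thigh (cm, assumed) | 0.5 × arm | 0.5 × thigh | Disputed redness (cm) |
|---|---|---|---|
| 24 / 45 | 12 | 22.5 | 12 to 22.5 |
| 30 / 55 | 15 | 27.5 | 15 to 27.5 |
| 38 / 65 | 19 | 32.5 | 19 to 32.5 |

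Example with 30 / 55: redness of 20 cm is 20/30 = 67% of the arm and 20/55 = 36% of the thigh. With repeated medication it is grade 3 by Appendix 4 and grade 2 by section 4.1.1. Without repeated medication it is grade 2 and grade 1. Only the first pair crosses the primary cut-off.

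**2. Exposure by group.** From the regimen table in the Summary of Trial, DNAx3 has 3 DNA-C visits × 2 thighs = 6 thigh injections per participant, and DNAx2 has 2 × 2 = 4. With 70 per group and full adherence that is 420 against 280.

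**3. Leakage induration, intradermal row.**

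| Diameter | 1, 3 or 6 days | 7 days |
|---|---|---|
| 1 cm | grade 1 | grade 1 |
| 1.5, 2 or 3 cm | none | grade 2 |
| 3.1 or 5 cm | none | grade 3 |

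A 1 cm induration lasting one day is graded. A 5 cm induration lasting six days is not.

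**4. Superficial or fluid-filled blistering.** 0.5 cm is grade 1, 1 and 2 cm are grade 2, and 2.1 and 4 cm have no grade.

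**5. Do steps 3 and 4 reach the primary endpoint?** The primary question is whether an event is grade 3 or above. Leakage induration of 5 cm for six days fails the written duration condition for grade 3. A superficial blister of 4 cm is not full-thickness loss. Read literally, both are not grade 3. What is undefined is their place among the lower grades.

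**The case against.** A reader might infer that parts of the primary safety endpoint cannot be scored at all. The documents do not support that for induration or blistering. The endpoint is binary, and the ungraded lesions fail the stated grade 3 criteria. Nor is all short-lived induration ungraded: induration arising in the muscle is always grade 3, and the gap is confined to leakage, which section 2.3.1 tries to prevent by choosing needle length for each participant.

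A reader might also infer that a seven-day diary card cannot show induration lasting more than 6 days. That fails too. Section 2.3.2 asks for at least 7 days of recording and keeps contact until solicited events resolve.

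Three further defences deserve weight.
- **Central review.** The Operational Sub-Group reviews the grades and unresolved queries go to the Trial Coordinating Committee (section 8.2). This limits drift between centres, so it cannot be assumed that each centre will improvise. It does not supply the missing rule.
- **The general scale in Appendix 4.** It covers events that the tables do not specify, and a size and duration with no cell might be read that way. But induration and blistering are named in the tables, and the general scale grades on activity and intervention, so the same kind of lesion would be graded on two bases.
- **Section 4.1.1 is the trial-specific rule for redness.** This is the natural reading, but the same sentence also refers the grading to Appendix 4, and nothing says which prevails.

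**Conclusion.** The point holds, with limited reach. The arm or thigh conflict is the only part that crosses the primary grade 3 cut-off. It needs thigh redness within the disputed band, roughly 12 to 32.5 cm across the assumed limb sizes, together with symptoms needing repeated medication. Such reactions are probably uncommon, although the protocol gives no rate. The imbalance of 6 against 4 thigh injections means that any misgrading would not fall evenly on the two groups. Because section 7.7.2 acts on 3 participants, a few cases could matter.

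The induration and blister gaps are certain on the text, but they mainly distort the grade 1-2 endpoint and the maximum-grade tables. The conclusion rests on reading section 4.1.1 as the circumference of the injected limb, and on reading a lesion that fails the grade 3 wording as not grade 3.

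**What to change.** - Reconcile the erythema wording of Appendix 4 with section 4.1.1 so that one limb reference applies to each injection site. Both circumferences are already measured at screening.
- Have the sponsor make the leakage-induration and superficial-blister rows exhaustive and monotone, so that each lesion has exactly one grade. The thresholds, and the role of duration, are for the sponsor to decide; this review proposes none.
- Before analysis, regrade affected reactions from the centimetre measurements of redness, blisters and hard swelling on the diary card (Appendix 5). The card does not record lesion depth or whether induration arose in the muscle, so those judgements must come from the clinical record.

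The cost is an edit to one appendix table and a limited regrade. Some reactions now ungraded will be counted, so reported local reactogenicity may rise. Depending on how the cells are filled, grade 3 counts could also change, so the sponsor must check the effect on the rules in sections 5.4.1 and 7.7.2 before adopting the wording.

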### Appendix 5 Diary Card

#### Guide for grade of general reaction

|                                        | Grade 1
mild                                                       | Grade 2
moderate                                                     | Grade 3
severe                                             | Grade 4
Extreme |
|----------------------------------------|-------------------------------------------------------------------------------|---------------------------------------------------------------------------------|-----------------------------------------------------------------------|----------------------------|
| Chills/rigors                   | Mild hot/cold flush requires blanket or occasional aspirin/paracetamol | Limiting daily activity >6 hours, or need regular aspirin/paracetamol | Uncontrollable shaking, treatment from doctor needed           | Hospitalisation     |
| Malaise/abnormal tiredness      | Normal activity reduced – not bad enough to go to bed                  | Fatigue such that ½ day in bed for 1 or 2 days                           | Fatigue such that in bed all day or ½ day for more than 2 days | Hospitalisation     |
| General (all over) muscle aches | No limitation of activity                                              | Muscle tenderness, limited activity e.g. difficulty climbing stairs      | Severe limitation e.g. can't climb stairs                      | Hospitalisation     |
| Headache                        | No treatment or responds to paracetamol like treatment                 | Regular paracetamol like treatment needed                                | Regular strong painkillers treatment needed                    | Hospitalisation     |
| Nausea                          | Intake maintained                                                      | Intake reduced less than 3 days                                          | Minimal intake 3 days or more                                  | Hospitalisation     |
| Vomiting                        | Less than 4 x a day or lasting less than 1 week                        | At least 4 x day or lasting 1 week or more                               | Unable to keep any food or fluids down                         | Hospitalisation     |

- Complete at approximately the same time every day ONLY on days that you are NOT going to clinic
- Fill in temperature and record the grade of other general reactions (use the table above as a guide)
- Add any comments regarding other symptoms
- Record any medication taken including over the counter medicines and anything taken to relieve local reactions
- Record the grade, or size in cm, of local reactions overleaf
- Please contact a member of the trials staff as soon as possible if you experience any symptoms of grade 3 or 4
- When the diary card is complete, please return it to a member of trials staff at your next visit

|                                                               | 12 hrs      | Day 1       | Day 2       | Day 3       | Day 4       | Day 5       | Day 6       | Day 7       |
|---------------------------------------------------------------|-------------|-------------|-------------|-------------|-------------|-------------|-------------|-------------|
| General Symptoms                                       |             |             |             |             |             |             |             |             |
| Date                                                   |             |             |             |             |             |             |             |             |
| Temperature °C                                         |             |             |             |             |             |             |             |             |
| Chills/rigors                                          |             |             |             |             |             |             |             |             |
| Malaise/ tiredness                                     |             |             |             |             |             |             |             |             |
| General muscle aches                                   |             |             |             |             |             |             |             |             |
| Headache                                               |             |             |             |             |             |             |             |             |
| Nausea                                                 |             |             |             |             |             |             |             |             |
| Vomiting                                               |             |             |             |             |             |             |             |             |
| COMMENTS
<hr/> <hr/> <hr/> <hr/>                    |             |             |             |             |             |             |             |             |
| Medication – list all medications and total daily dose |             |             |             |             |             |             |             |             |
|                                                               | Dose | Dose | Dose | Dose | Dose | Dose | Dose | Dose |
| 1                                                      |             |             |             |             |             |             |             |             |
| 2                                                      |             |             |             |             |             |             |             |             |
| 3                                                      |             |             |             |             |             |             |             |             |

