### **5.4.1 Recommendations for discontinuation**

Discontinuation of the study vaccine schedule due to an adverse event is at the discretion of the site Principal Investigator or their Medical Deputy, but would be recommended in the event of a grade 3 or 4 clinical or laboratory event (confirmed on examination or repeat testing respectively) which did not resolve within 72 hours. There must be no further immunisations following:

- 1) extensive, indurated redness and swelling involving the major circumference of the arm or thigh, not resolving within 72 hours or
- 2) fever  $\geq 39.5^{\circ}\text{C}$  within 48 hours; anaphylaxis; bronchospasm; laryngeal oedema; collapse; convulsions or encephalopathy within 72 hours

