### 7.7.2 Indications for discontinuation of immunisations in all participants

If 3 or more participant experience grade 3 or 4 adverse events attributed to the same product, then further recruitment to the Clinical Trial and immunisations with that product will be discontinued pending an unblinded review of all safety data by the

DSMC. Following this review the DSMC will make a recommendation to the Trial Coordinating Committee about continuation of the trial. The sponsors will formally decide to terminate or not the clinical Trial.

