| Itching or irritation at the site                                                                               |        |       |       |       |       |       |       |       |       |       |       |       |       |       |       |       |
| Redness/discolouration (cm)                                                                                     |        |       |       |       |       |       |       |       |       |       |       |       |       |       |       |       |
| Fluid filled blisters (cm)                                                                                      |        |       |       |       |       |       |       |       |       |       |       |       |       |       |       |       |
| Blood filled blisters (cm)                                                                                      |        |       |       |       |       |       |       |       |       |       |       |       |       |       |       |       |
| Hard swelling in skin surface at or close to site (cm)                                                          |        |       |       |       |       |       |       |       |       |       |       |       |       |       |       |       |

Diary

[figure not shown]

|                            |                              |   |   |   |
|----------------------------|------------------------------|---|---|---|
| Date of birth       |                              |   |   |   |
| Trial number        |                              |   |   |   |
| Trial centre        |                              |   |   |   |
| Vaccination number  | 1                            | 2 | 3 | 4 |
|                            | Please circle as appropriate |   |   |   |
| Date of vaccination |                              |   |   |   |

|                         |
|-------------------------|
| Contact details: |
|                         |
|                         |

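### The diary card's only call instruction depends on a grade that temperature, redness and hard swelling never receive on the card

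*Protocol*

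**What the plan says.** Protocol Appendix 5 gives participants one trigger for contacting staff between visits: "Please contact a member of the trials staff as soon as possible if you experience any symptoms of grade 3 or 4". The same instructions set temperature apart from the graded items, "Fill in temperature and record the grade of other general reactions", and let skin findings be entered as a measurement, "Record the grade, or size in cm, of local reactions overleaf". The relevant local rows are "Redness/discolouration (cm") and "Hard swelling in skin surface at or close to site (cm"). The completed card is handed in at the next visit.

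Section 5.4.1 lists two absolute bars to further dosing, introduced by "There must be no further immunisations following". The first is "extensive, indurated redness and swelling involving the major circumference of the arm or thigh, not resolving within 72 hours". The second includes fever of 39.5°C or more within 48 hours, alongside clinical events such as anaphylaxis and convulsions.

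Two trial-level rules depend on grade 3-4 events becoming known. Section 7.7.1 calls an extra committee meeting for certain events confirmed on attendance or repeat testing and unresolved at 72 hours. Section 7.7.2 pauses recruitment and the product: "If 3 or more participant experience grade 3 or 4 adverse events attributed to the same product".

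Outside the card, section 2.3.2 provides a verbal explanation and continuing contact by the clinical team as events evolve. For a raised temperature, section 4.1.2 advises only that daily readings continue until it is normal.

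**The concern.** A call rule that depends on grade works only for symptoms the participant can grade. Someone at home with 40°C has a reading but no grade for it on the card, and section 4.1.2 does not list temperature among the symptoms that participants grade. Redness is graded in section 4.1.1 and Appendix 4 as a share of limb circumference together with symptoms, while the card asks for centimetres. Muscle induration is grade 3 on the clinician's judgement, so it needs an examination.

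The rows left out are the ones that bear on the two mandatory stops a participant could detect at home. At stake are prompt contact and examination, and timely counting towards sections 7.7.1 and 7.7.2. For example, a fever that lasts beyond 72 hours but clears before the next scheduled visit could not be confirmed on attendance at that visit.

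**Working it through.** The plan gives no figure to reproduce. The check compares the card's rows with its grading guides, then uses the visit schedule to see what a missing call would delay.

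**Card rows (Appendix 5)**

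| Block | Rows | With a grade guide | Without |
|---|---|---|---|
| General | 7 | 6: chills, malaise, muscle aches, headache, nausea, vomiting | 1: temperature |
| Local | 6 | 2: pain, itching | 4: redness, fluid blisters, blood blisters, hard swelling |
| Total | 13 | 8 | 5 |

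Of the 5 ungraded rows, 3 (temperature, redness, hard swelling) bear on the section 5.4.1 stops.

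**Planned doses (Summary of Trial, 70 per group)**

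- DNA-C: 70 × 3 + 70 × 2 = 350.
- NYVAC-C: 70 × 1 + 70 × 2 = 210.
- Total: 350 + 210 = 560.

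**First scheduled visit after each dose (section 2.6, dose on its nominal day)**

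| Dose | Next visit | Nominal day | Window |
|---|---|---|---|
| DNA-C, week 0 | week 1 ± 1 day | 7 | days 6-8 |
| DNA-C, weeks 4 and 8 | weeks 5 and 9 ± 3 days | 7 | days 4-10 |
| NYVAC-C, weeks 20 and 24 | weeks 22 and 26 ± 1 week | 14 | days 7-21 |

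The nominal visit falls 7 − 3 = 4 days after the 72-hour mark for DNA-C, and 14 − 3 = 11 days after it for NYVAC-C.

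**Does the individual dosing stop survive?**

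- Doses followed by another dose: group 1 at weeks 0, 4 and 8 = 70 × 3 = 210; group 2 at weeks 0 and 4 = 70 × 2 = 140; group 2 at week 20 = 70. Total 420.
- Of these, 210 + 140 = 350 have their first visit at nominal day 7, and 70 at nominal day 14. Each has a scheduled visit before the next dose, so dated card entries are available in time to apply section 5.4.1.
- Final doses, week 24 in both groups: 560 − 420 = 140. No later dose exists; only examination and the section 7.7 counts are affected.

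**Would printing the Appendix 4 fever grades be enough?**

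- The section 5.4.1 limit in °F is 39.5 × 9/5 + 32 = 103.1°F.
- The °C ranges in Appendix 4 put 39.5°C in grade 2 (39.0-39.7°C); grade 3 starts at 39.8°C.
- The °F ranges put 103.1°F in grade 3 (103-105°F).

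The card uses °C. A grade rule based on the °C ranges would still not prompt a call from 39.5 to 39.7°C, although the mandatory stop already applies there. An explicit 39.5°C limit covers both the stop and every grade 3-4 fever in the °C column.

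**The case against.** The strongest reply is that the card is not the only channel. Section 2.3.2 promises a full verbal explanation and contact until solicited events resolve, and fever and skin reactions are solicited events. The participant information sheet and one figure in the diary appendix are not visible, and either might carry a call limit. This limits the finding to the card. But section 2.3.2 states no temperature or size, and contact guided by how events evolve presupposes that staff know of the event.

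Second, section 5.4.1 is a rule for investigators, not a call rule for participants, and no dosing decision changes. That is correct: the dosing stop holds for all 420 doses with a later dose.

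Third, the local rows add little to early counting. Under Appendix 4, redness is not grade 3 without irritation needing repeated medication. Skin induration must exceed 3 cm and last more than 6 days. Muscle induration is left to the clinician. This also stands: the effect on counting is mainly about fever. For redness and swelling the loss is prompt examination.

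Fourth, the harm is delay. Diary entries enter the safety analysis, and section 7.7.2 has no attendance condition, so a fever recorded at home still counts, only later. Section 7.7.1 is narrower still, because the event must also be unexplained and unexpected. The frequency is unknown, and the Introduction reports no grade 3 events in EV01, where 20 volunteers were allocated NYVAC. These points keep the severity low but do not make the call rule usable for the ungraded rows.

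**Conclusion.** The finding holds, as a minor point about a participant-facing form. On the visible card, 5 of 13 symptom rows cannot activate the only call instruction, and 3 of those 5 bear on stops that section 5.4.1 makes mandatory. The consequence is possible late contact and late counting, nominally until day 7 after DNA-C (350 planned doses) or day 14 after NYVAC-C (210 planned doses). Individual stopping, sample size and efficacy analyses are unaffected.

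The dose counts show where the gap could matter, not how often calls would be missed; the protocol does not say how often a trigger would be met. The conclusion assumes that the participant relies on the card alone, that no other graded symptom is severe at the same time, and, for the timing, that doses fall on their nominal days.

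**What to change.** Extend the contact line on the card with: *or if your temperature is 39.5°C or more, or if redness or hard swelling extends round most of the arm or thigh*. Have staff give the same limits in the verbal explanation under section 2.3.2.

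The temperature and extent follow section 5.4.1. The 48- and 72-hour conditions are left out deliberately so that the call comes at onset. Clinicians would still grade from the recorded sizes. The wording is not meant to catch smaller muscle induration, which needs examination, and it sets no limit for the two blister rows.

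The cost is a reprinted card, one added point in the verbal explanation, and some extra calls from participants.
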